#### Overall well-being of the family

The Parental Stress Index (PSI) is a self-reported inventory designed to measure parental experiences of stress in relation to the parent–child interaction. It has six child subscales and seven parent subscales. In the Healthy Start project, a modified Swedish version [15] was included, as an elaboration of the parental part of the questionnaire. The questions included information on perceived changes in life since the child was born with regard to factors such as sleep, work, stress, life satisfaction, conflicts with spouse, and worries. Moreover, one question asked if the parent thought he/she had enough time together with the child.

#### General questions about the family and its relations

This section of the parental questionnaire included information on paternal, maternal, and child ethnicity, whether the parents were living together, number of siblings, household income, chronic physical diseases in the child, mental diseases in the child, and estimated general physical health of the child.

#### Paternal and maternal basic information

Both the mother and father were asked if he or she was the biological parent of the child, and about their heights and weights, their highest completed educational level, occupation, average number of work hours per week, average number of hours per week spend outside the home without the child per week, as well as their level of physical activity per week.

#### Biological samples

During the last or second to last visits we sampled hair and saliva from children and their parents in the intervention- and the control group.

Hair was sampled from each child and both parents to obtain an objective measure of chronic stress. Long-term cortisol can be used as an indicator of both sub-acute and chronic stress, as analysis of cortisol in hair potentially gives a non-invasive measurement of long-term activity in the HPA-axis [16]. It has previously been found that hair from human individuals may be used as an integral measure of cortisol production in the past 3–6 months [17]. As hair grows approximately 1 cm per month, it is estimated that the first cm of hair (from the scalp) contains cortisol from the previous month, whereas the next one cm of hair contains cortisol from two months back and so on [17]. Information on frequency of hair washes and whether the hair was currently colored was also obtained, in order to adjust for potential dilution of the cortisol level. Compared to subjective measurements of stress derived from inventories, the hair analyses may provide a more accurate measure of chronic stress level, by estimating cortisol over the previous 1–6 months. The measure may hence be used to study how chronic stress may affect the body [16], and in particular the risk of developing overweight and obesity. Cortisol will be extracted from hair using the Elisa method [18]. The biochemical extraction of cortisol is still on-going, but is expected to be ready fall of 2012.

#### Saliva

Saliva samples for each child and both parents were also collected, using Oragene OG-500 and OG-575. OG-500 was used for the parents and children who were able to spit on their own. They were asked to spit 2 ml in a tube, which was afterwards closed and shaken for 5s.

OG-575 was used for children who were not able to spit on their own. A swab was placed and moved in cheek pouch along the gums and inner cheeks to absorb as much saliva as possible. The swab was then placed in a v-notch of funnel, and saliva was wringed out of v-notch into the tube. The tube was then closed and mixed for 5 s. DNA is currently being extracted from the samples and specific SNP analyses or GWAS will be performed later in relation to candidate genes related to obesity and weight gain, food dependency, appetite, hunger and satiety, physical activity and sedentariness, stress coping or sleep quality (melatonin and clock genes).

#### Actigraph GT3X

As a means of validating the questionnaire information, objective information on daily activity as well as sleep duration and sleep quality was obtained on a subgroup of the intervention children over 5 days/nights (n = 79) half way through the intervention period, using Actigraph GT3X. Actigraph catches a person’s movements triaxial through an accelerometer on one single axis or multiple axes. The device catches movements between 0.25 Hz – 2.3 Hz, as previous studies have found that voluntary movements take place within this range [19]. Specifically, information on sleep efficiency (sleep/number of hours spend in bed), time the child went to bed, time the child got out of bed, time asleep, awakenings, sleep onset, minutes awake, average duration of awakening and sleep latency, was obtained. The child was asked to wear the Actigraph for 5 successive days, and the parents were instructed that if the child did not want to wear the device all the time, the most important time to wear it was during the night. Moreover, parents were asked to complete a sleep diary for the same days that the Actigraph was worn. The device was placed on the left wrist (right wrist if the child was left-handed) using an elastic band. If the elastic was too big for the wrist, it was placed on the upper arm or the ankle (left ankle if the child was right-handed and vice versa). Actigraph GT3X was also used for obtaining objective information on physical activity over five consecutive days (n = 79). The device was set to an epoch length of 60 s with normal filter level.

Finally, from all included children (intervention- and both control groups), information and measures of various factors during the child’s first years of life is available from a clinical database which visiting nurses from 12 municipalities from the Copenhagen area have established. This clinical database includes standardized records with information on breast-feeding, exposure to passive smoking, maternal health, decreased ability to care for the child because of alcohol or other substance abuse, network in the family, remarks about the child’s signals and reactions (sleep, anxiety, crying), and growth during the child’s first years of life. Information from this database will be obtained by linkage with the CPR-numbers.

### Power calculation

With a power of 90%, alpha of 0.05 and 275 individuals in each group, it will be possible to detect a difference between the intervention- and control groups of 0.28 SD in BMI. For a 7-year old boy with a height of 1.25 m (equivalent to the mean height for 7-year old children in 1980–1983), a 0.28 SD BMI corresponds to a difference in BMI = 0.45 kg/m^2^, or 0.70 kg body weight between the intervention and control groups. With 80% power and a significance level of 5%, we will be able to demonstrate differences of 0.5 BMI units between the intervention and control group children. We greatly oversampled in relation to the main outcome (BMI) to secure sufficient numbers post-intervention and in relation to more specific outcomes such as body fat and fat free mass.

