#### Stress of the child

To assess behavioral difficulties and stress in the child, the Danish version of the Strengths and Difficulties Questionnaire (SDQ) was included as an integrated part of the parental questionnaire. SDQ is a behavioral screening questionnaire that consists of 25 items on prosocial behavior and emotional and behavior problems. Scores on 5 scales are derived from these 25 items: emotional symptoms (5 items), conduct problems (5 items), hyperactivity/inattention (5 items), peer relationship problems (5 items) and pro-social behavior (5 items) [13]. The SDQ has been translated into the different Nordic languages, and has so far been completed for nearly 100,000 children in the Nordic countries during the past years [14].

Table 2 shows the pre-intervention distribution of age, height, weight, BMI, waist circumference, hip circumference, sum of 4 skinfolds, percentage body fat, energy intake, carbohydrate intake, protein intake, fat intake, sugar intake, sleep latency, SDQ-score, and household income by group. *T*-test analyses showed a statistically significant difference in total SDQ-score between the intervention group and the control group (Table 2). No other significant differences in baseline characteristics between the intervention group and the control group were found (Table 2).

**Table 2 T2:** Pre-intervention distribution of selected covariates by group

	**Intervention group**			**Control group**			**P (**** *t* ****-test)**
	**n**	**Mean**	**SD**	**n**	**Mean**	**SD**	
**Age (years)**	271	4.0	1.1	272	4.0	1.1	1.00
**Height (cm)**	271	104.3	9.2	272	104.5	9.1	0.77
**Weight (kg)**	271	17.4	3.1	272	17.6	3.0	0.45
**BMI (kg/m**^ **2** ^**)**	271	15.9	1.0	272	16.0	1.0	0.12
**Waist circumference (cm)**	253	51.8	3.2	257	52.1	3.0	0.22
**Hip circumference (cm)**	252	55.5	3.6	255	56.0	3.9	0.19
**Sum of 4 skinfolds (mm)**	236	24.6	5.4	242	24.8	5.2	0.67
**Body fat (%)**	199	22.3	10.1	176	21.3	8.9	0.33
**Energy intake (MJ)**	237	4.7	1.0	244	4.8	1.0	0.15
**Carbohydrate intake (gr./day)**	237	158.0	36.0	244	164.1	35.3	0.06
**Protein intake (gr./day)**	237	42.8	11.2	244	44.6	10.3	0.07
**Fat intake (gr./day)**	237	38.1	10.1	244	38.1	11.2	0.96
**Sugar intake (gr./day)**	237	56.2	16.5	244	58.5	16.5	0.12
**Sleep latency (minutes)**	250	18.3	14.5	256	18.6	13.9	0.84
**SDQ-score (points)**	253	7.1	3.9	256	6.4	4.0	0.05*
**Household income (thousands, DKK)**	217	870	622	231	788	306	0.07

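### The 80% power figure (0.5 BMI units) is larger than the 90% figure (0.45 kg/m²) for the same comparison; both cannot hold on the one sample size and implied SD given

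*Protocol article*

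**What the plan says.** The Power calculation section of the protocol article makes two statements about the intervention-control comparison of BMI, which it calls the main outcome.

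- **At 90% power.** "With a power of 90%, alpha of 0.05 and 275 individuals in each group", the section says, "it will be possible to detect a difference between the intervention- and control groups of 0.28 SD in BMI". It converts this for a 7-year-old boy 1.25 m tall: "a 0.28 SD BMI corresponds to a difference in BMI = 0.45 kg/m^2^, or 0.70 kg body weight".
- **At 80% power.** "With 80% power and a significance level of 5%, we will be able to demonstrate differences of 0.5 BMI units", again between intervention and control children. This sentence gives no sample size and no SD.

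The section closes with a remark on numbers after the intervention: "We greatly oversampled in relation to the main outcome (BMI) to secure sufficient numbers post-intervention". It gives no attrition rate and no expected number of completers.

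**The concern.** Lower power at the same sample size, SD and alpha means that a smaller difference can be claimed as detectable. The section goes the other way: power falls from 90% to 80% and the detectable difference rises from 0.45 to 0.5 kg/m². A reader who takes the two sentences together, with the only sample size given, has to conclude that one of them is wrong or rests on inputs that are not shown.

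These sentences are the article's only statement of the trial's sensitivity on BMI. They are what a reader would use to judge which effects a null result makes unlikely. That matters here because the Background cites a pooled effect of prevention programmes of only 0.15 kg/m².

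**Working it through.** **Inputs**

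- 275 per group, alpha 0.05, 90% power, 0.28 SD = 0.45 kg/m² (Power calculation)
- 80% power, 5% significance, 0.5 BMI units (Power calculation)
- Implied SD: 0.45 / 0.28 = 1.607 kg/m². This is derived; the article does not state it.
- Assumption: two-sided test and equal groups, normal approximation. The article does not state sidedness; two-sided is the choice that reproduces its figure.

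**Formula.** Detectable difference = (z₀.₉₇₅ + z_power) × √(2/n) × SD, with √(2/275) = 0.08528.

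**Step 1: reproduce the 90% statement**

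- (1.9600 + 1.2816) × 0.08528 = 0.276 SD, stated as 0.28.
- 0.276 × 1.607 = 0.44 kg/m², stated as 0.45. The gap comes from rounding 0.276 up to 0.28.
- Weight conversion: 0.45 × 1.25² = 0.70 kg, as stated.

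The 90% statement is sound.

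**Step 2: the 80% statement on the same inputs**

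- (1.9600 + 0.8416) × 0.08528 = 0.239 SD.
- 0.239 × 1.607 = 0.38 kg/m², against 0.5 stated.
- Power for a true 0.5 kg/m²: 0.5 / 1.607 = 0.311 SD; Φ(0.311 / 0.08528 − 1.96) = Φ(1.69) = 0.954, about 95%.

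**Step 3: a check that needs neither n nor SD.** For any common n and SD, the 80% and 90% detectable differences stand in the ratio 2.8016 / 3.2416 = 0.864. So 0.45 at 90% goes with about 0.39 at 80%, and 0.5 at 80% goes with about 0.58 at 90%. The stated pair has a ratio of 0.5 / 0.45 = 1.11.

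**Step 4: can another reading of the inputs give 0.5?**

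| Reading | 80% detectable difference |
|---|---|
| Rounding of 0.28 and 0.45 (SD 1.56 to 1.65) | 0.37 to 0.40 kg/m² |
| One-sided test (0.212 SD) | 0.34 kg/m²; at 90% it gives 0.250 SD, so it does not fit that statement either |
| 271 per group, about the number enrolled (0.241 SD) | 0.39 kg/m² |
| SD 1.0, the baseline BMI SD in both groups in Table 2 | 0.24 kg/m² |

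None of these reaches 0.5.

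**Step 5: what would give 0.5 at 80% power**

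- With SD 1.607: n = 2 × (2.8016 × 1.607 / 0.5)² = 162.2, so 163 per group, which is 41% below 275.
- With 275 per group: SD = 0.5 / 0.239 = 2.09 kg/m².

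The article states neither.

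**The case against.** The strongest defence is that the 80% sentence never says it reuses 275 per group. The next sentence speaks of oversampling to keep enough children after the intervention, so 0.5 may have been worked out for an expected completer sample. The article contains a number of roughly that size. Biological samples says hair was taken at the last or second-to-last visits in both examined groups, and the Discussion mentions around 350 children sampled. Split evenly, that is 175 per group, and 2.8016 × √(2/175) × 1.607 = 0.48 kg/m², which rounds to 0.5. A condensed article might leave the attrition assumption to the full protocol.

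This stands as a possible explanation, and it is why 0.5 cannot be called a plain slip. It remains inference: children who gave hair need not be the completers, the even split is assumed, and the power section ties 0.5 to no reduced sample. As printed, the two sentences still conflict.

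The defence is also right about consequences. On the printed inputs, 0.5 understates the trial's sensitivity. No sample size, analysis or decision rule rests on it, and a 90% figure that reproduces stands beside it.

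A reader might infer more: that the sample size is unsound, or that 0.5 is definitely 30% too high (0.5 / 0.384 = 1.30). The article supports neither. The 275 per group agrees with the 90% statement, and the 30% holds only if 275 per group and SD 1.61 were the inputs intended for the 80% sentence.

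**Conclusion.** The point holds as a minor correction. The article gives one sample size and one implied SD. On these, 0.45 kg/m² at 90% power and 0.5 at 80% power are incompatible; the 80% figure would be 0.24 SD, or 0.38 kg/m² (0.37 to 0.40 allowing for rounding), and 0.5 would have about 95% power.

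The conflict in direction depends only on the two sentences sharing n, SD and alpha. The figure of 0.38 rests further on SD 1.61, which is back-calculated from two rounded numbers for an illustrative 7-year-old; with the Table 2 baseline SD of 1.0 it would be 0.24. The discrepancy is conservative. It affects how the trial's sensitivity is described, not whether 275 per group is adequate for the stated 90% target.

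**What to change.** First establish which inputs lie behind 0.5, then change the one sentence accordingly:

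- **If 275 per group and SD 1.61 were intended:** restate the 80% figure as 0.24 SD (0.38 kg/m² at SD 1.61), with two-sided alpha 0.05.
- **If 0.5 rests on a smaller post-attrition sample or a larger SD:** keep 0.5 and state that n and SD in the sentence. On the present figures this means about 163 per group at SD 1.61, or an SD of about 2.09 at 275 per group. Under either, the matching 90% figure is about 0.58 kg/m², so the sentence should make clear that its inputs differ from those behind 0.45.

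The cost is one sentence. Design, conduct and analysis are unaffected.

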### Intervention

The intervention consisted of four main areas: optimizing dietary intake and physical activity quantity and quality, improving sleep duration and quality, and reducing chronic stress of the child and the family by improving interaction between child and parents. The intervention was planned and organized according to each participating family’s individual needs and resources. Thus, the intervention was not administered as a standardized package that was more or less identical for all participants. Based on primarily the dietary record and the parental questionnaire, the consultants evaluated the specific needs of each family, and subsequent consultations were planned to include one or more of the four themes (ex. intake of sugar, intake of vegetables, physical activity outside day-care, bed time routines etc.). This evaluation was also based on the themes each family was motivated to work with, using the “stages of change” motivational models. Translational assistance was not provided by the project, and consequently non-Danish speaking individuals were not able to participate.

The main focus of the intervention was on the family as a whole and not only on the child. Stages of change principles and motivational interviewing were used as the framework for the counseling process [20], and the main concept was to improve the family’s knowledge and action. Motivational interviewing (MI) is a psychotherapeutic method that is evidence-based and is applicable across a wide variety of problem areas including health behavior change [21]. MI uses a guiding style to engage with people, clarify their strengths and aspirations, evoke their own motivations for change, and promote autonomy of decision making [22], and was applied to enhance personal motivation for change. In the stages of change model, change is a process involving progress through a series of stages. MI was used to help families to proceed through these stages [23].

Each consultation started with asking the family if they had any themes they wanted to discuss, and how problems or agreements had progressed since the previous consultation. In addition to the consultations, families in the intervention group were invited to participate in bi-monthly cooking classes and monthly play (activity) classes. The idea behind these classes was to inspire the participants to convert the theory from the consultations into practice, to motivate the family to spend more time together and to network with other families. The cooking classes had various themes, such as using fish in the meals, healthy fast food, healthy desserts etc.

Keywords for each of the four main intervention areas were prepared to support the health consultants in their planning of the consultations. For these keywords, tools to change behavior in a given direction were created, and together with the consultant each family then decided which tools they wanted to work with until next consultation. Examples of tools are presented in Table 3.

**Table 3 T3:** Examples of tools compi led from the key words selected within each intervention focus area

	**Diet**	**Physical activity**	**Sleep**	**Stress**
**Example of tools**	· Make fruit a part of breakfast or dessert in the lunch package	· Plan activities with the whole family together	· Avoid that the child uses computer games, internet or watches TV before bedtime	· Prepare the child of what will happen during the day
	· Supply the lunch · package with small tomatoes, carrot sticks etc.	· Go with the bike, for a walk or play outside with your child	· Avoid that the child watches TV-programs catered for adults	· Build up every-day routines
	· Replace the sugary cereals with oatmeal	· Restrict screen time to 2 hours per day	· Increase the physical activity level of the child during daytime	· Distinguish between work- and free time, so the child knows when it has the parent’s full attention
	· Eat natural yoghurt and add with fruits of your own choice		· Provide clear rules and routines around bedtime	· Be physically active with your child every day
	· Restrict intake of sweets, but when provided, use for instance fruit sorbet as an alternative to ice cream, fruit as an alternative to sweets etc.		· Avoid a stressed environment in the home	
	· Keep a jug of water in the refrigerator, and refresh the water with lemon slices, fresh mint leaves or frozen fruit			

The keywords for the four main areas were:

#### Dietary intake

The chosen keywords were based on the Danish national recommendations, “The 8 Dietary Advices”. Each of the 8 dietary advices were included, but adjusted to the age of the target group (2–6 years). Thus, examples of the key points were:

· Eat fruit and vegetables, 300–500 grams per day, depending on the age

· Eat fish or fish filling several times per week

· Eat potatoes, rice or pasta and whole grain bread every day

· Go easy on sugar, especially from soft drinks, sweets and cake

· Go easy on fat, especially from dairy products and meat

· Eat from all food categories every day, choose various products within each food category

· Quench your thirst with water, 1-1½ liter per day

· Be physically active, at least 1 hour per day [24]

#### Physical activity

Based on current literature, examples of the selected key points were:

· Increase parental physical activity and interaction. Children who are physically active with their parents are more active than children who are not [25]

· Increase time spend outdoor. Children who spend more time in outdoor play spaces are more active than children who spend less time outdoor [25]

· Reduce sedentary behavior. TV viewing and sedentary behavior may be associated with physical activity in children [25]

#### Sleep

Based on current literature, the selected keywords were:

· Reduce time spend on computer games, internet and both active and passive TV-watching before bedtime [26,27]

· Increase daytime physical activity level [28]

· Improve the sleep environment in the home. It seems that clear rules and routines around bedtimes improve children’s sleep quality, whereas the presence of parents while the child is falling asleep has the opposite effect [29]

· Improve the emotional environment in the home. Parental stress has been shown to be associated with poor sleep quality [30]

#### Stress

A literature search showed that social isolation, attendance in full-day pre-school [31] and major life events [32] were important determinants of psychological stress in the child. Moreover, a high level of parental stress was linked to insecure child attachment and parental unresponsiveness, both of which are known to induce psychological stress in the child [33]. Thus, some of the key points in this part of the intervention were:

· Increased parental awareness of the stress-level

· Attention to being present when being with the child

· Increased physical activity

· Tranquility to quiet playing

· Physical contact, e.g. plays, sports and massage [34]

As it emerges from Table 3, the various parts of the intervention were often integrated – i.e. focusing on the area of physical activity may additionally benefit sleep quality and reduce the stress level of the child.

### The team

The daily project team consisted of a research director, a project leader and three health consultants. Trainees and student workers were connected to the project continuously. Moreover, the project had supervision from statisticians, psychologists and dieticians on designing and carrying out the study.

### Data cleaning

Data was entered into the Epidata system and subsequently cleaned.

Baseline data was cleaned first by going through all questionnaires, dietary records, measurements and notes from the consultations, and comparing information from the paper forms with information in the database. This comparison was conducted for six variables, which were selected based on a high proportion of missing information. Then, information from questionnaires, dietary records and measurements from 5% of the participants was re-entered, and it was decided to accept an error rate of 2%. The same procedures will be performed with follow-up data.

